### Adherence

As HOMESIDE dyads live complex lives, it is unlikely that all dyads will adhere to the 12-week intervention. Adherence to the MI/RI intervention will be measured first through CG completed diaries, collecting the number of sessions and the time per session per week. If a dyad supplies a range (e.g. 20–30 min) for the time in a diary entry, the lower limit (i.e. 20 min) will be used for the duration of that day. For dyads with incomplete or missing entries in the diary, we will use the information from the phone call guidelines to measure adherence to the intervention, collecting how often they have been using the programme at each phone call in weeks 2, 5, 7, 9 and 11.

At any given week during the intervention, dyads are deemed adherent if they have reported a minimum of 2 sessions in the completed diaries across the intervention period (i.e. 7 to 90 days post-randomisation). The first week will not be included in the calculation of adherence as it includes the first training session, which may have been held at the end of the week for some dyads. Adherence to the intervention will be derived by summing the number of weeks dyads are deemed adherent across the intervention period. Dyads will be deemed adherent if they scored at least 10 (i.e. a minimum of 10 weeks in which they adhered) and did not have more than two consecutive weeks in which they do not report any engagement with the programme. For dyads who may not be adherent due to incomplete or missing information in the diary, we will use the data captured in the phone call guidelines and consider the dyad adherent if they answered that they have been using the programme 2 days per week or more at all 5 weeks.

Information on the current use of music and reading in daily life at follow-up at 90 and 180 days post-randomisation, irrespective of the randomised intervention, will be summarised by treatment group.

### Analysis populations

The analysis set will consist of all dyads who were randomised, with all dyads reported and analysed according to their randomised study arm. The safety population will consist of all dyads receiving at least one study treatment (including SC alone), with all dyads reported and analysed according to the intervention received. Participants in the MI or RI arms will be considered as having received the study treatment if the dyad attended at least one training session and that all training components were delivered (meeting the fidelity criteria).

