### Design

HOMESIDE is a large international pragmatic, three-arm parallel-group RCT. Dyads consisting of the PwD and cohabitating CG were randomised to one of the three arms: MI plus SC, RI plus SC or SC alone. HOMESIDE is a superiority trial, with the hypothesis that MI plus SC is superior to SC alone (primary) and RI plus SC (secondary) in relation to BPSD at 90 days post-randomisation. Online assessments occurred at each MI/RI instruction session and follow-up at 90 and 180 days post-randomisation (Fig. 1). The study was prospectively registered at the Australian New Zealand Clinical Trials Registry (ACTRN12618001799246, registered on 05 November 2018) and ClinicalTrials.gov (NCT03907748, registered on 09 April 2019).

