### Intervention groups

The interventions were described fully in the detailed published protocol [9]. In brief, the MI involved a 2-h home-based training session in which a qualified music therapist instructed the CG on methods and strategies for using music to assist with care and connection with the PwD. This training covered activities such as singing or listening to familiar or preferred songs and engaging in dialogues about these with the PwD, movement to music and playing instruments. The RI involved a 2-h home-based RI instruction session delivered by a qualified practitioner to engage the PwD during and following the RI. The training covered the CG reading aloud to the PwD, the PwD reading aloud to the CG, listening to audiobooks, playing word games and discussion of the text. Following training, CGs were instructed to deliver the MI or RI at least five times per week for 30 min over a 12-week period. CGs allocated to SC alone were instructed to care for the PwD in their usual manner.

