### Safety outcomes

The number and percentage of PwD and CGs who experience adverse events will be summarised across the intervention period (i.e. randomisation to 90-days post-randomisation), the follow-up period (i.e. 90-days post-randomisation to 180-days post-randomisation) and study period (i.e. randomisation to 180 days post-randomisation) by each intervention group. The total number of events will be reported for the PwD and CG separately.

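### The as-treated safety population ties receipt of MI or RI to training fidelity, so exposed dyads with incomplete training have no stated place in the safety tables

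*SAP article*

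**What the plan says.** Two sets are defined under Analysis populations. For effectiveness: "The analysis set will consist of all dyads who were randomised, with all dyads reported and analysed according to their randomised study arm". For safety, the set is "all dyads receiving at least one study treatment (including SC alone), with all dyads reported and analysed according to the intervention received".

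The same section then says when an MI or RI participant has received the study treatment: the dyad must have "attended at least one training session and that all training components were delivered (meeting the fidelity criteria". Both conditions must hold.

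The later Safety outcomes section (under Effectiveness analysis) summarises adverse events "by each intervention group" over three periods that begin at randomisation or at day 90. It gives no grouping rule of its own, so the definition under Analysis populations governs.

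**The concern.** A safety set grouped as treated is meant to follow exposure. In this trial, exposure is what the caregiver does at home after training: "Following training, CGs were instructed to deliver the MI or RI at least five times per week for 30 min over a 12-week period". Whether the trainer covered every component does not settle whether the person with dementia was exposed.

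Under the stated rule, a dyad with one undelivered component that went on to use music at home for 12 weeks has not received MI. Its adverse events then have no stated place in the MI column. This matters most for events judged likely or very likely due to the intervention, which the article lists as a safety outcome. Such an event in a low-fidelity dyad could appear in no column, or possibly under the comparator.

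The exclusion could also be informative. A session cut short because the person with dementia was unwell or distressed would leave components undelivered. The document does not show how often this happened, so it is a possibility and not a finding.

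**Working it through.** **Reading the rule through**

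1. Membership (Analysis populations): "The safety population will consist of all dyads receiving at least one study treatment (including SC alone".
2. Grouping (same section): "with all dyads reported and analysed according to the intervention received".
3. Receipt of MI or RI (same section): attendance and full delivery of components to fidelity.
4. Take a dyad randomised to MI that attended a session with a component missing. By step 3 it has not received MI, so by step 2 it cannot be grouped under MI.
5. Two destinations remain: outside the safety set, or under SC. The second is conceivable because every arm contains SC (Design: "Dyads consisting of the PwD and cohabitating CG were randomised to one of the three arms: MI plus SC, RI plus SC or SC alone") and step 1 names SC alone as a study treatment. The article chooses neither.
6. Neither of the two Safety outcomes sections contains a rule that would keep the dyad under MI.

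**Comparison with Adherence.** That section classifies dyads by weeks with at least two reported sessions and sets no fidelity condition. A dyad can therefore be adherent to MI there and not have received MI under Analysis populations.

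**An ambiguity that affects size.** Table 1 schedules training on Days 1, 21 and 42. The phrase about all training components may refer to one attended session or to the whole programme. On the first reading, a dyad with one flawed and one complete session still qualifies. On the second, a dyad that stopped after Day 1 does not.

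**Design figure, used as the denominator.** Sample size gives a difference of 3, SD 7.5, two-sided 5%, 90% power and 20% attrition. Per arm, n = 2 × (1.960 + 1.282)² × 7.5² / 3² = 131.3, rounded up to 132. Then 132 / 0.80 = 165, and 3 × 165 = 495. The stated figures reproduce. The point does not depend on them.

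**Illustration of counts.** The document gives no fidelity-failure rate and no event rate, so all rates here are assumed.

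- Failure in 5%: 0.05 × 165 ≈ 8 dyads per active arm. Failure in 20%: 0.20 × 165 = 33.
- If 30% of these have at least one event: 8 × 0.30 ≈ 2 and 33 × 0.30 ≈ 10 dyads with events lost from an active arm's column.

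**Illustration of percentages.** Let k dyads with e events leave a column of N dyads with E events.

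- Dropped: the MI percentage becomes (E − e)/(N − k). It is unchanged if e/k = E/N, falls if e/k is higher and rises if it is lower.
- Moved to SC: the SC percentage becomes (E_SC + e)/(N_SC + k). It changes only if e/k differs from E_SC/N_SC.
- With the same 30% rate everywhere, no expected percentage moves.
- With assumed rates of 20% (MI and RI, including the affected dyads) and 10% (SC), and the affected dyads of both active arms moved to SC:

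| Fidelity failure | SC dyads | SC percentage | Difference from 20% |
|---|---|---|---|
| 0% | 165 | 10.0% | 10.0 points |
| 5% | 165 + 2 × 8 = 181 | (16.5 + 3.2)/181 = 10.9% | 9.1 points |
| 20% | 165 + 2 × 33 = 231 | (16.5 + 13.2)/231 = 12.9% | 7.1 points |

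Counts in the MI and RI columns can only fall or stay the same. A shift in percentages needs a difference in rates that the document does not supply.

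**The case against.** The strongest reply has four parts.

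- **Serious events are described elsewhere.** Primary estimand attributes lists hospitalisation and death of either dyad member as intercurrent events and promises the number and percentage of dyads with intercurrent events by treatment arm. No fidelity condition is attached there. This stands and narrows the point mainly to related and non-serious events. It is not a full substitute for the safety table, because the article does not say that each event type will be shown separately.
- **Nothing says these dyads go under SC.** A reader might infer that exposed dyads are counted as standard care. The mention of SC alone can equally mean only that the SC arm belongs to the safety set. This stands: the article is silent on their destination.
- **No bias in favour of the interventions is shown.** A reader might infer one. Lower counts are certain if any affected dyad had an event, but percentages move only if event rates differ, and the direction depends on how. This stands.
- **The tables are descriptive.** No safety test or decision rule is planned, and all effectiveness analyses use every randomised dyad. This stands and limits the severity.

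None of these replies supports fidelity as a criterion for exposure or gives the affected dyads a place.

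**Conclusion.** The point holds as a defect in a stated definition. Applied as written, the rule takes dyads that attended MI or RI training with a component undelivered out of the MI or RI safety columns, and the article does not say where they go. MI and RI event counts can only fall or stay the same.

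The effect on percentages cannot be determined in size or direction. The figures of 8 to 33 dyads per active arm, and 2 to 10 with events, rest wholly on assumed rates and on the planned 165 per arm. The number affected also depends on which reading of all training components is meant. Only the descriptive safety tables are affected. This should be fixed, but it does not threaten the trial's main conclusions.

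**What to change.** In Analysis populations, define the MI (or RI) safety group as every dyad that attended at least one MI (or RI) training session, in whole or in part, and remove the fidelity condition. Report fidelity separately by arm. Also tabulate adverse events by randomised arm, so that every randomised dyad appears in at least one safety table.

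Attendance is a better criterion than any reported music or reading session. The article itself (Adherence; Baseline dyad characteristics) records music and reading in daily life whatever the allocation, so reported use does not separate the arms cleanly.

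The cost is one revised sentence and one extra table. No new data should be needed, since the current definition already relies on attendance and fidelity records. The Introduction says that changes before unmasking will be tracked and that the final plan is signed before the code is broken, so the correction can be prespecified if made by then.

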### Trial population

#### Trial profile

The flow of dyads through the study will be presented in a Consolidated Standards of Reporting Trials (CONSORT) flow diagram, comprising the number of dyads screened, eligible, consented, randomised and received the allocated intervention. The number of dyads as well as the reasons for exclusion, withdrawal and lost to follow-up will also be reported in the CONSORT diagram.

#### Baseline dyad characteristics

Demographic and baseline variables for both PwD and CG will be summarised and presented by each study arm. Dyads will be described with respect to age, sex, site, marital status, highest level of education, current or last job occupation, main source of income and their current use of music and reading in daily life. Other baseline variables include dementia diagnosis, severity of dementia, time of onset dementia, length of time having dementia (PwD only) and CG’s relationship and length of relationship with PwD will also be reported. Categorical data will be summarised using frequencies and percentages. Continuous variables will be summarised using means and standard deviations, or medians and quartiles (25th and 75th percentiles) for asymmetrically distributed continuous variables.

## Analysis

### Outcome variables

#### Person living with dementia

The primary BPSD outcome of the study is the NPI-Q severity of the PwD at 90 days post-randomisation. Secondary outcomes include NPI-Q severity at 180 days post-randomisation, quality of life (measured by the Quality of Life-Alzheimer’s Disease [QoL-AD]) at 90 and 180 days post-randomisation, depression (measured by Montgomery-Asberg Depression Rating Scale [MADRS]) at 90 and 180 days post-randomisation and cognition (measured by Mini-Mental State Examination Score [MMSE]) at 90 days post-randomisation.

#### Caregiver

Outcomes for the CG include distress (measured by NPI-Q distress), quality of life (measured by Assessment of Quality of Life-6D [AQoL-6D] instrument), depression (measured by Patient Health Questionnaire-9 [PHQ-9]), resilience (measured by 14-item Resilience Scale [RS-14]), sense of competence (measured by Short Sense of Competence Questionnaire [SSCQ]) and the quality of caregiver-patient relationship (QCPR questionnaire) at 90 and 180 days post-randomisation.

#### Safety outcomes

Safety outcomes for both PwD and CG include at least one adverse event, at least one related adverse event (defined as likely or very likely occurred due to the intervention), at least one serious adverse event (hospitalisations or death) and at least one non-serious (other) adverse event.

## Effectiveness analysis

### Primary estimand

The estimand for HOMESIDE is defined according to the addendum to the ICH E9 on estimands and sensitivity analysis in clinical trials [13]. HOMESIDE aims to answer the specific research question: does the addition of music therapy to SC in a home setting delivered by a CG to PwD, compared to SC alone over 90 days, improve BPSD of the PwD, as measured by the mean difference in NPI-Q severity, regardless of the post-randomisation (intercurrent) events listed below, while assigning the worst possible NPI-Q score to the PwD who died.

#### Primary estimand attributes

Treatment: MI added to SC compared to SC alone (control), allocation by randomisation.Population: Adults with diagnosed dementia who are residing at home with a caregiver (e.g. sibling, spouse, adult child) who is not paid to deliver care. Full details of the inclusion and exclusion criteria are provided in the protocol [9].Variable: NPI-Q severity at 90 days post-randomisation.Intercurrent events: Possible intercurrent events are outlined below and will be handled using the treatment policy strategy except for death of the PwD for which the composite strategy will be used by assigning the worst-possible NPI-Q score (i.e. 36). Where possible, outcome data will be collected after each of these intercurrent events occur. If no data is collected after an intercurrent event, we will assume that the participant’s outcome after the intercurrent event will be similar to that of all other participants (see details in reporting and methods for missing data).A dyad receiving a different treatment to what they were allocated toRelocation of PwD to a care homeA dyad no longer cohabitatingA change in primary carerDeath of either the PwD or primary carerNew medication taken by the PwD or CG (any post-baseline that will affect the trial outcome; see section on concurrent medications for details)Hospitalisation of either the PwD or CGUnplanned or planned surgery or dental work for either the PwD or CGCOVID-19 without hospitalisation of either the PwD or CGPopulation-level summary: mean difference in NPI-Q severity between arms (MI + SC and SC alone).

The number and percentage of dyads who had intercurrent events will be described overall and by treatment arm.

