### Randomisation

Dyads were randomly allocated to one of the three intervention groups with a 1:1:1 allocation using a computer-generated schedule of randomly permuted blocks, stratified by site (Queensland [Australia], Victoria [Australia], Germany, Norway, Poland and the UK) to achieve a balance between the arms within each stratum. The list was created by an independent statistician and uploaded to the randomisation module of the REDCap (Research Electronic Data Capture) trial database hosted at the University of Melbourne [10]. The study aimed to have equal numbers of participants within each country. However, due to recruitment challenges at some sites, other sites increased their recruitment target to maximise recruitment. Participating dyads could not be fully blinded due to the active nature of the interventions. The assessors and biostatisticians were blinded to the allocation during the conduct of the trial and will not be unblinded until the database is ready for breaking of the code.

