### Sample size

The trial was designed to recruit a total of 495 dyads (165 per arm) to detect a difference of 3 points in NPI-Q total severity score between the MI plus SC and SC alone at 90 days post-randomisation. This assumes 90% power, a two-tailed significance level of 5%, an equal standard deviation of 7.5 points in the groups, no correlation between baseline and 12 weeks (conservative) and 20% attrition. A 3-point change from baseline in NPI-Q total severity score is considered a clinically meaningful difference [11]. No interim analyses to stop the trial early were planned, and no interim analysis was conducted.

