### Primary outcome

The estimate corresponding to the primary estimand of the NPI-Q severity of the PwD at 90 days will be obtained from a likelihood-based longitudinal data analysis model, with responses consisting of all scores (baseline, 90 and 180 days post-randomisation) [14]. The model will include factors representing intervention (SC, MI + SC, RI + SC), time, intervention by time interaction with the restriction of a common baseline mean score across interventions and unstructured variance–covariance among repeated measurements. The model will adjust for the stratification variable (site) used during the randomisation and will be referred to as the unadjusted model. Recruitment site includes Northern Australia, Southern Australia, Norway, the UK, Poland and Germany. The model will include the SC alone group as the reference group.

In sensitivity analysis, variables known to be prognostic of NPI-Q severity (i.e. type of dementia, gender of PwD and CG’s relationship with PwD) will be included in the unadjusted longitudinal data analysis model. This model will be referred to as the adjusted model. The treatment effect estimated from the unadjusted and adjusted models will be the mean difference in NPI-Q severity from baseline to 90 days post-randomisation between the MI plus SC versus SC alone groups.

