### Reporting and methods for missing data

Most outcome variables are derived from combining multiple items from a questionnaire to create a score. Therefore, if one or more of the items within the score has a missing response, this affects the derivation of a score for the participant. The number of items missing within an outcome variable will be examined and reported. Decisions on how to handle the missing data will be based on recommended practice for deriving these outcomes, where available. According to recommended practice, if there are two or less items with missing responses in the QoL-AD, MADRS and PHQ-9 instruments, they should be replaced with the mean of the participant’s responses across the complete items [15–17]. Similarly, this replacement will be done by dimension in the AQoL-6D instrument if there is one item with a missing response for that dimension [18]. If there are four or less items with missing responses in the MMSE questionnaire, they should be replaced with the mean of the participant’s responses across the complete items [19]. For all other outcomes combining questionnaire items, if a participant has a missing response to one or more item needed to derive the outcome, the participant will be classified as having a missing outcome.

Following the handling of missing data in outcomes (described above), the primary strategy to handle missing continuous study outcomes will be a likelihood-based approach (i.e. constrained longitudinal data analysis). This approach assumes that the probability of missing data on the study variable is not related to the missing data but to some of the observed measured data in the model (missing at random).

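### Known deaths scored 36 enter one missing-at-random model, so PwD known to be alive but unscored get a share of the 36s; MI versus SC is biased to the extent that death or living-dropout rates differ by arm

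*SAP article*

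**What the plan says.** Under Primary estimand, the target is the mean NPI-Q severity difference at 90 days, regardless of the listed intercurrent events, with the worst score given to PwD who died. Primary estimand attributes makes death of the PwD the one exception to the treatment policy strategy: the "composite strategy will be used by assigning the worst-possible NPI-Q score (i.e. 36"). The same section assumes that anyone without data after an intercurrent event has an outcome like that of the other participants. It does not confine the comparison to the living.

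Under Primary outcome, the estimate comes from a "likelihood-based longitudinal data analysis model, with responses consisting of all scores" (baseline, 90 and 180 days). Reporting and methods for missing data leaves remaining gaps to the same likelihood: "This approach assumes that the probability of missing data on the study variable is not related to the missing data", but to observed data in the model. The only sensitivity analysis named for the primary outcome adds covariates to this model.

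The Sample size section plans for "no correlation between baseline and 12 weeks (conservative) and 20% attrition".

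**The concern.** Once deaths are scored 36, a known death always has a day-90 value, while a living PwD who drops out has none. Whether the value is missing then depends on the value itself, even given arm, site and baseline. For dropouts known to be alive, the missing-at-random assumption therefore fails because of the plan's own scoring rule. The model predicts their day-90 score from an arm mean and covariance that include the 36s, although under the estimand a living person keeps their own score.

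This is a separate matter from whether 36 is a suitable score. At stake are the primary contrast, if deaths or dropout differ by arm, and its precision in any case. The adjusted and subgroup models inherit the problem, so no planned analysis would reveal it.

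**Working it through.** **The plan's own figure.** The trial was sized at "a total of 495 dyads (165 per arm") "to detect a difference of 3 points in NPI-Q total severity score". "This assumes 90% power, a two-tailed significance level of 5%, an equal standard deviation of 7.5 points in the groups". Per arm: 2 × (1.960 + 1.282)² × 7.5² / 3² = 131.3, so 132; 132 / 0.8 = 165; × 3 = 495. The figure reproduces (power 90.1% with 132 per arm).

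**Inputs.** From the SAP: score 36, SD 7.5, n = 165 per arm, baseline correlation 0, overall attrition 20%. Assumed, because the SAP gives no figures: death proportion p, dropout m among the living by arm, and mean μ among the living (10 in SC; range 8 to 14). The 20% is applied to the living, on top of deaths. All deaths are taken as known; this is relaxed under the objection.

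**Weight of deaths in an arm.** The target mean is 36p + (1-p)μ. The planned model replaces p by w = p / [p + (1-p)(1-m)]. With p = 0.03 and m = 0.20, w = 0.03 / 0.806 = 3.72% instead of 3.00%, so each death counts 1.24 times. With μ = 10, the arm mean is 26 × 0.0072 = 0.19 too high.

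**Bias of MI minus SC.** The bias per arm is (36-μ)(w-p).

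| Deaths MI / SC | Living dropout MI / SC | Effect among the living | True | Planned | Bias |
|---|---|---|---|---|---|
| 3% / 3% | 20% / 20% | none | 0 | 0 | 0 |
| 3% / 3% | 20% / 20% | -3 | -2.91 | -2.89 | +0.02 |
| 2% / 4% | 20% / 20% | none | -0.52 | -0.64 | -0.12 |
| 3% / 3% | 25% / 15% | none | 0 | +0.12 | +0.12 |
| 3% / 3% | 30% / 10% | none | 0 | +0.24 | +0.24 |

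For the last row, w is 0.03/0.709 = 4.23% in MI and 0.03/0.903 = 3.32% in SC, and 26 × 0.0091 = 0.24. With this dropout pattern, no effect, deaths of 1-6% and living means of 8-14, the bias runs from +0.07 to +0.49.

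**Check on the three-visit model.** A constrained longitudinal model with unstructured covariance was fitted by EM to 200,000 simulated dyads per arm, at correlation 0.5 and with deaths by day 180 also set to 36. Contrast bias was -0.003 (equal rates), -0.18 (deaths 2% versus 4%) and +0.35 (dropout 30% versus 10%). The last fell to +0.24 with no deaths after day 90, and to +0.22 when half of the dropouts returned at day 180.

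**Precision, correlation 0, equal arms, 3% deaths, 20% dropout, no effect.**
- Planned, variance per arm: [(1-w)7.5² + w(1-w)26²] / (165 × 0.806) = 78.37 / 133.0 = 0.589; SE of the contrast = √(2 × 0.589) = 1.086.
- Two-part (known death fraction plus living mean): 0.03 × 0.97 × 26² / 165 + 0.97 × 7.5² / (165 × 0.8) = 0.119 + 0.413 = 0.533; SE = 1.032.
- Ratio 1.052. Its square, 1.107, means about 11% more dyads for the same precision.

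The SE ratio is 1.022 at 1% deaths and 1.071 at 5%. At an assumed correlation of 0.5, simulation put the excess at 3-9%.

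**Power with a 3-point effect among the living, 3% deaths, 20% dropout.** Planned: 2.89 / 1.106, 74%. Two-part: 2.91 / 1.046, 79%.

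**The case against.** **The contrast is a difference, so the over-weighting largely cancels.** This stands. A reader might infer that MI versus SC is biased in any case, or always against MI. The table supports neither: bias is 0 to 0.02 with equal rates, and its sign depends on which arm has more deaths or dropout. Unequal dropout is plausible, because only MI and RI ask caregivers for sessions at least five times a week, but the SAP gives no figures by arm.

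**Not every dropout is known to be alive.** This also stands and limits the remedy. Table 1 schedules recording of deaths to day 180, but the article does not say that vital status is traced after withdrawal. Take 3% deaths, dropout 30% versus 10% unrelated to death, and vary the share of dropouts' deaths that become known. Treating every dropout not known to be dead as alive then has its own bias:

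| Share known | Planned model | All such dropouts treated as alive |
|---|---|---|
| 100% | +0.24 | 0 |
| 50% | +0.12 | -0.08 |
| 0% | 0 | -0.16 |

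So one cannot say that only living PwD can be missing, or that imputing from survivors always removes the bias.

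**The assumption is declared.** True: the SAP states it openly, so this is not two passages contradicting each other. But a declared assumption that fails for participants known to be alive still leaves the estimator off the stated estimand.

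**The sizes are modest and rest on assumptions.** Fair. A bias of 0.24 is 8% of the 3-point target, and at 3% deaths it moves type I error from 5% to about 5.5%.

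**Conclusion.** The point holds for PwD known to be alive at day 90 but without a score. Deaths are over-weighted within each arm whenever there are both deaths and living dropouts (3.7% instead of 3.0% at 3% deaths and 20% dropout). The contrast bias is conditional on arm differences: about 0 with equal rates, -0.12 with deaths 2% MI versus 4% SC, and +0.12 to +0.24 with the unequal dropout examined at 3% deaths. The SE is about 2-7% larger at 1-5% deaths under the plan's zero correlation.

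Death rates, dropout by arm and the living mean are assumptions, and the calculation takes deaths as fully known. A reader might also blame the whole shortfall from 90% power on the over-weighting. That is not supported: at 3% deaths the fall from 90% to about 79% comes from the composite score itself, and the over-weighting takes it on to about 74%. This is a worthwhile, cheap improvement to the primary analysis, not a fatal flaw.

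**What to change.** In Primary outcome and in Reporting and methods for missing data, fix the order of steps:

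1. For PwD known to be alive at a visit but without a score, multiply impute NPI-Q by arm from living participants' baseline, other visit and site.
2. For dropouts of unknown vital status, do not assume survival. Impute vital status by arm first, then give 36 or a survivor score accordingly. Report their number by arm.
3. Set known deaths to 36, fit the planned baseline-constrained model to each completed data set and combine by Rubin's rules.

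An alternative to multiple imputation for the known-status part is arm mean = 36 × proportion dead + (1 - proportion dead) × survivor mean from the longitudinal model, with a bootstrap confidence interval.

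Use the same order in the adjusted and subgroup models, and keep the current direct-likelihood fit as a sensitivity analysis.

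Cost: SAP wording and modest programming before the code is broken, after which the SAP treats changes as post hoc. No new data are needed and the estimand is unchanged. The downsides are that multiple imputation replaces a single model fit, and that the result depends on how well vital status is ascertained.
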